### Outcomes

The primary outcome is Angina Scale and TCM syndrome score according to the guiding principles of clinical research technology of traditional Chinese medicine and natural medicine in the treatment of coronary heart disease and angina pectoris. The higher the score, the more severe angina pectoris and symptoms. The secondary outcomes are based on the Seattle Angina Questionnaire (SAQ), another scale of angina; three scales will be collected at baseline, 4, 8, and 12 weeks after randomization. Serum total cholesterol [13], triglyceride [14], high-density lipoprotein cholesterol (HDL-C), low-density lipoprotein cholesterol (LDL-C), non-high-density lipoprotein cholesterol (non-HDL-C), apolipoprotein [8] A-I, ApoA-II, ApoB, lipoprotein-a, and the proportions of related biochemical parameters, including TC/HDL-C, non-HDL-C/HDL-C, and ApoB/Apo A-1, endothelin (ET), nitric oxide (NO), prostaglandin E (PGE), calcitonin gene-related peptide (CGRP), hypersensitive-C-reactive-protein (hs-CRP), and tumor necrosis factor α (TNF-α); the results of transthoracic Doppler echocardiography (TTDE), including left ventricular end-diastolic diameter (LVEDD), left ventricular end-systolic diameter (LVESD), left atrium (LA), interventricular septal thickness (IVST), left ventricular posterior wall (LVPW), fractional shortening (FS), and left ventricular ejection fraction (LVEF); an electrocardiogram (EKG) will be measured and collected at baseline and 12 weeks after randomization.

Safety outcomes are blood routine examination and laboratory liver and renal function test results, including aspartate aminotransferase (AST), alanine aminotransferase (ALT), alkaline phosphatase (ALP), blood urea nitrogen (BUN), creatinine (CR), and uric acid (UA). Adverse events will be monitored at each visit. The investigators will evaluate the degree of adverse events and whether they are related to the intervention, and they will ensure that the adverse events are properly resolved. All collected adverse events and subsequent medical intervention will be recorded in the CRF.

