**Methods/design:**

This is a prospective randomized controlled trial. The trial will enroll 150 patients with MVA. On the basis of Western drug treatment, patients will be randomized into two groups, and the experimental group will receive QJHX treatment for 12 weeks and follow-up at 24 week. The primary indicators are the clinical efficacy of angina pectoris and the evidence of traditional Chinese medicine (TCM) efficacy. Secondary indicators are the Seattle Angina Scale score, serum lipid levels, electrocardiogram, and echocardiogram diagnosis. Additional indicators are endothelial function and immunoinflammatory factors. Adverse events will be monitored throughout the trial.

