### Sample size

According to the results of a previous single-center clinical observation, after 12 weeks of treatment with QJHX, the effective rate was 85.7% in the treatment group and 60.1% in the control group. According to the sample calculation decoction, the number of samples is *n* = 61 cases in each group. In the decoction, *p*_*1*_ and *p*_*2*_ are the estimated values of the two population rates, respectively, *p* is the combined rate, *p* = (*p*_*1*_ + *p*_*2*_)/2, when *α* = 0.05, *β* = 0.10, *u*_α_ = 1.96, and *u*_β_ = 1.282 in the double test and bilateral test. The sample size was 75 cases in each group, a total of 150 cases, taking into account a 20% drop-off rate.
$$ {\mathrm{n}}_1={n}_2{\frac{\left[ ua\sqrt{2p\left(1-p\right)}+ u\beta \sqrt{p_1\left(1-{p}_1\right)+{p}_2\left(1-{p}_2\right)}\right]}{{\left({p}_1-{p}_2\right)}^2}}^2 $$

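### The primary outcome is declared as two severity scores, but the sample size and its 90% power rest on one undefined binary effective rate that is tied to neither scale

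*Protocol article*

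**What the plan says.** Three sections of the protocol article describe the primary outcome or the effect the trial is sized on.

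- **Outcomes:** "The primary outcome is Angina Scale and TCM syndrome score according to the guiding principles of clinical research technology". It adds that higher values mean worse disease and symptoms. The scales are collected at baseline and at weeks 4, 8 and 12. No responder definition, cut-off or primary visit is given.
- **Abstract, Methods/design:** "The primary indicators are the clinical efficacy of angina pectoris and the evidence of traditional Chinese medicine (TCM) efficacy".
- **Sample size:** a previous single-center observation is the source, and "after 12 weeks of treatment with QJHX, the effective rate was 85.7% in the treatment group and 60.1% in the control group". The formula is for two proportions: p1 and p2 "are the estimated values of the two population rates". With two-sided α = 0.05 and β = 0.10 the result is "61 cases in each group", raised to 75 per group (150 in total) for 20% dropout.

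Two other places bear on the point. The closing paragraph of the Discussion lists an angina score and a TCM score among the efficacy indicators whose changes will be observed. Statistical analysis gives t tests or the Mann-Whitney test for continuous variables and chi-square or Fisher's exact test for categorical ones, without saying which kind the primary outcome is.

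**The concern.** A power statement belongs to one variable, measured at one time and analysed in one way. Here the declared variables are two severity scores, while the powered variable is one binary response that Outcomes does not mention. A reader cannot tell whether the confirmatory result will be a difference in scores or a difference in response rates. If it is a rate, it is not clear whether it comes from the Angina Scale or the TCM syndrome score.

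This matters more than usual here. The control group receives the background treatment alone and no placebo is described, so the trial is apparently open-label, with symptom-based outcomes. Which result counts as confirmatory should therefore be beyond dispute before the arms are compared. Trial status reports 83 patients recruited of the planned 150, so at the time of the article this could still be settled.

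**Working it through.** **1. Reproduce the plan's figure.** Inputs from Sample size: p1 = 0.857, p2 = 0.601, u_α = 1.96, u_β = 1.282. The mean rate is p = (0.857 + 0.601)/2 = 0.729.

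n = [1.96·√(2·0.729·0.271) + 1.282·√(0.857·0.143 + 0.601·0.399)]² / (0.857 − 0.601)²

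= [1.96·0.6286 + 1.282·0.6020]² / 0.256²

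= 2.0037² / 0.06554 = 61.26.

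The plan's 61 is this value rounded down. Power for the two rates is 89.9% at 61 per group. The planned 75 per group less 20% leaves 75 × 0.8 = 60 evaluable, with power 89.4%. (Strictly, 61/0.8 = 76.25, so 77 per group; the gap from 75 is immaterial.) The arithmetic is sound for a binary outcome.

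**2. Try to carry it over to the scores.** A comparison of mean scores needs an expected difference and a standard deviation. The article gives neither for either scale, so no single power figure exists for the outcome as declared.

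**3. What can be said without them.** For two means, two-sided 0.05 and 90% power, the detectable standardised difference is d = (1.96 + 1.282)·√(2/n):

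- n = 60 per arm (75 less 20%): 3.242 × 0.1826 = 0.59 SD.
- n = 75 per arm: 3.242 × 0.1633 = 0.53 SD. This applies if everyone randomised is analysed, because Recruitment plans intention-to-treat with last observation carried forward for discontinuers.

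**4. Range under assumed differences.** The values of d below are assumptions, not figures from the article (normal approximation, two-sided 0.05).

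| Assumed d (SD) | Power at 61 per group | Evaluable per group for 90% power |
|---|---|---|
| 0.3 | 38% | 234 |
| 0.4 | 60% | 132 |
| 0.5 | 79% | 85 |
| 0.6 | 91% | 59 |
| 0.7 | 97% | 43 |

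The same 61 per group is far too few or more than enough depending on a quantity the article does not state.

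**5. Look for a link between rate and scores.** Outcomes refers to external guiding principles but gives no cut-off. Sample size does not name the scale behind the rate. The Abstract's wording would fit a response rate but defines none. No section makes the connection.

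**The case against.** The strongest reply is that the effective rate is simply the scores converted to response under the guideline that Outcomes cites, and that the Abstract's efficacy wording confirms it. That reading is open and cannot be excluded, since the guideline is not at hand. It limits the finding: what is shown is a link that is not stated, not proof that a different outcome was powered. It does not remove the finding, because even on that reading Outcomes names the wrong form of the variable, and the article does not say which scale the rate belongs to.

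Other replies stand in part:

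- **Time point.** Week 12 is well supported: the powered rate is at 12 weeks and treatment lasts 12 weeks. Outcomes does not label a primary visit, but this is a small gap.
- **Choice of test.** Assigning a test to each endpoint is commonly left to an analysis plan, so the generic list in Statistical analysis is not itself a fault. A reader might infer that the headline result will be picked after the data are seen. The article alone cannot establish that.
- **Nature of the scales.** Outcomes does not give their range. A graded or ordinal scale is possible, so the SD-based figures assume a score that is reasonably treated as continuous.

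A reader might also infer that the trial is comfortably powered for the scores. If the rate were a single cut of a normal score with equal variance in both arms, 85.7% against 60.1% would correspond to a shift of about 0.81 SD, needing 2 × (3.242/0.811)² ≈ 32 per arm. That is an illustration under an assumption no section supports. It should not be used to judge this trial's power, or how much information a response rate would lose.

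**Conclusion.** The concern holds as an inconsistency in the primary outcome. The stated 61 per group and 90% power are correct for a comparison of two proportions and do not apply to the two severity scores as declared.

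It would be tempting to conclude that the trial is underpowered. The documents do not support that: with no mean difference or standard deviation, power for the scores is unknown in either direction. What can be stated is the detectable difference at 90% power and two-sided 0.05, about 0.59 SD with 60 evaluable per arm or about 0.53 SD with all 75 analysed. Both assume a roughly continuous score and a two-group comparison of means.

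The practical consequence is that the confirmatory result is not identified. That needs correcting before any comparison by arm.

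**What to change.** By amendment, before any comparison by arm, name one primary variable at week 12 and use the same wording in the Abstract, Outcomes and Sample size. Either of two repairs is coherent:

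- **(a) Keep the rate.** Define effective, name the scale it comes from, and declare that rate at week 12 as the primary outcome. The existing calculation then stands.
- **(b) Keep a score.** Name which one, and restate the sample-size paragraph as the standardised difference that 150 patients can detect at 90% power and two-sided 0.05: about 0.59 SD with 60 evaluable per arm, or about 0.53 SD if all 75 per arm are analysed. Say which analysis set the figure refers to. A detectable difference is not evidence that such a difference is likely, so the sponsor should add the expected difference and SD if the earlier single-center data provide them.

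Under either repair, state what becomes of the other scale, since the Abstract and Outcomes both give angina and TCM measures primary status. It can be secondary, or co-primary with a stated rule on whether both or either must succeed. If it is co-primary, the sample-size paragraph must reflect that rule, because the present calculation covers a single comparison.

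The cost is amendment wording, with no extra patients, visits or measurements. The registry entry was not available for this review, so the sponsor should check whether it needs the same change.

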### Interventions

Eligible participants will be randomized to either the test group or the control group. According to the patient’s condition, the following primary treatments will be selected: antiplatelet drugs (such as aspirin), statins, β-blockers, calcium antagonists, and nitrates. Participants in the control group will receive primary treatment, while QJHX plus primary treatment will be applied in the test group.

The TCM decoction is a compound preparation of Chinese herbs, whose ingredients are equivalent to *Astragalus propinquus*, *Polygonatum sibiricum*, *Ziziphi spinosae*, and *Panax notoginseng*; 10 herbals in total, packaged in a unit of 3 g. QJHX will be produced by Jiangyin Tianjiang Pharm Co. Ltd. (approval number AH20160363), Jiangsu, China. Drugs will be packaged and distributed according to the random serial number in the drug distribution center.

The dosage, method, and frequency of administration will be explained to the participants orally and in writing. Participants will be instructed to take one pack (3.0 g) at a time, two times per day for 12 weeks. At each visit, the participants will receive the drugs for the next intervention, and the drugs left over from the previous intervention will be returned. The dose taken and the accordingly calculated medication compliance will be recorded in the CRF. The scheduled treatment time will be 12 weeks unless serious adverse events occur or the patient withdraws from treatment. During the observation period, the basic treatment of coronary heart disease is unchanged, and non-pharmacologic care is permitted. Other Chinese herbal medicines, Chinese patent medicines, and psychiatric medication are prohibited. If angina pectoris occurs, nitroglycerin tablets can be temporarily taken. Any combination of medications and doses for physical conditions will be recorded in detail. Any questions raised by participants will be answered to facilitate the completion of the trial. The detailed study schedule is shown in Fig. 2.

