### Statistical analysis

Continuous variables are expressed as mean ± standard deviation [16] or median (quartile range), depending on the nature of the distribution, and they will pass two-sample *t* tests (assuming normal distribution and equal variance), separate-variance *t* test (without assuming normal distribution and mean squared error), or the Mann-Whitney *U* test (without assuming normal distribution and mean squared error). Categorical variables are expressed as frequency and percentage, and they will be compared between groups by the chi-square test or Fisher’s exact test. Statistical analysis will be performed using SPSS 22.0 software.

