In conclusion, this paper presents a rigorously designed, randomized controlled clinical study protocol for the treatment of MVA with QJHX. In this study, we will observe the changes in safety indicators and efficacy indicators, such as angina pectoris score, serum lipids, ECG, cardiac ultrasound, TCM evidence score, and quality of life scale; vascular endothelial function indicators and immune and inflammatory factors; and the number of outpatient visits and hospitalizations due to symptom exacerbation by telephone follow-up after 6 months. The results of this study will provide a basis for a large-scale randomized controlled study to further evaluate the efficacy and safety of QJHX in the treatment of primary microvascular angina pectoris, to preliminarily elucidate the mechanism of action, and to accumulate information for preclinical studies of new drugs.

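### Compare week-12 nitric oxide with adjustment for baseline NO and baseline nitrate use, and read it only as supportive evidence on endothelial function

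*Protocol article*

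**What the plan says.** All references are to the protocol article.

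- **Outcomes** lists the blood markers "endothelin (ET), nitric oxide (NO), prostaglandin E (PGE), calcitonin gene-related peptide (CGRP", among others. They "will be measured and collected at baseline and 12 weeks after randomization".
- **Abstract, Methods/design** gives their role: "Additional indicators are endothelial function and immunoinflammatory factors". The closing paragraph of the **Discussion** repeats it ("vascular endothelial function indicators and immune and inflammatory factors") and says that the results will serve "to preliminarily elucidate the mechanism of action". NO is not labelled by name as an endothelial marker. That is the natural reading, because the Discussion's rationale for the herbs runs through NO and endothelial NO synthase.
- **Interventions** lets the background treatment be chosen from "antiplatelet drugs (such as aspirin), statins, β-blockers, calcium antagonists, and nitrates", according to the patient's condition, and holds it unchanged during observation. It adds: "If angina pectoris occurs, nitroglycerin tablets can be temporarily taken". Concomitant drugs and doses are recorded.
- **Randomization and concealment** stratifies by site only.
- **Statistical analysis** gives one generic rule for continuous variables: "they will pass two-sample *t* tests (assuming normal distribution and equal variance"), or an unequal-variance or rank-based alternative. It names no covariate.

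**The concern.** Organic nitrates act by releasing NO. This is general pharmacology and is not stated in the article. A circulating NO value in a recent user can therefore mix drug-derived and endothelial NO, and the stated comparison of raw values does not separate the two.

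The two kinds of nitrate use have different consequences:

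- **Maintenance nitrates** are in place at baseline, unchanged afterwards, and balanced on average by randomisation. They widen the spread of NO and cost power.
- **As-needed nitroglycerin** follows angina attacks after randomisation. If QJHX reduces attacks, patients in the test arm may take less of it. Drug-derived NO would then be lower in that arm because the treatment works, and this would offset part of any endothelial gain.

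At stake is the reading of one mechanistic marker.

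**Working it through.** **1. The plan's own figure.** The article gives no mean, SD or sample size for NO. Its only calculation is for the effective rate (Sample size: 85.7% v 60.1%, u-values 1.96 and 1.282). With p = (0.857 + 0.601)/2 = 0.729:

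n = [1.96√(2 × 0.729 × 0.271) + 1.282√(0.857 × 0.143 + 0.601 × 0.399)]² / 0.256² = 61.26

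The article states 61. With 75 per arm and 20% drop-off, 75 × 0.8 = 60 remain. These figures serve below only as a scale for power.

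**2. Noise from maintenance nitrates.** Assume that a share f of patients take them and that they shift NO by d, in units of the SD among non-users. Neither value is in the article.

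- Effect detectable with 90% power at 61 per arm: (1.96 + 1.2816) × √(2/61) = 0.587 SD.
- SD inflation: √(1 + f(1 − f)d²).
- Power after inflation: Φ(0.587 / (inflation × √(2/61)) − 1.96).

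| f | d | SD inflation | Power for 0.587 SD |
|---|---|---|---|
| 0.20 | 0.5 | 1.02 | 89% |
| 0.35 | 1 | 1.11 | 83% |
| 0.50 | 2 | 1.41 | 63% |

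**3. Possible bias from as-needed nitroglycerin.** Let D be the share of control patients with recent intake at the week-12 draw minus the share of QJHX patients, and let d now be the NO shift from recent intake. Then observed difference = true difference − D × d. Each cell shows the bias and, in brackets, what a true +0.30 SD would look like.

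| D | d = 0.5 | d = 1 | d = 2 |
|---|---|---|---|
| 0 | 0 (+0.30) | 0 (+0.30) | 0 (+0.30) |
| 5 points | −0.025 (+0.275) | −0.05 (+0.25) | −0.10 (+0.20) |
| 10 points | −0.05 (+0.25) | −0.10 (+0.20) | −0.20 (+0.10) |
| 20 points | −0.10 (+0.20) | −0.20 (+0.10) | −0.40 (−0.10) |

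Cancelling +0.30 SD needs D × d = 0.30, for example 15 points at 2 SD or 20 points at 1.5 SD. Within this range the sign cannot reverse when d is at most 1 SD (bias at most 0.20) or when D is 5 points (bias at most 0.10).

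A second setting uses a true effect of 0.50 SD and 60 per arm, where power without bias is 78%. With d = 1 SD and D = 10, 20 or 30 points, the observed effect is 0.40, 0.30 or 0.20 SD and power is 59%, 38% or 19%.

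**4. What adjustment can and cannot do.** Under a constant shift, a covariate for baseline maintenance nitrate use removes the f(1 − f)d² term in step 2. The SD returns to 1 and power to 90%. Adding baseline NO multiplies the remaining variance by about 1 − r², where r is the remaining correlation of baseline with week-12 NO (not given). Neither covariate touches the D × d term in step 3, because that arises after randomisation.

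**The case against.** The case against has several strong parts.

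- **Much of this may sit elsewhere.** Blood-draw conditions and biomarker covariates are often left to a laboratory manual or analysis plan that is not shown, and the statistical paragraph is generic. That stands for sampling conditions, and their absence is not criticised here. The point rests on the test that the article does state for continuous outcomes.
- **NO is a minor marker.** It is an additional indicator, listed beside ET, PGE and CGRP, and the mechanistic aim is worded as preliminary. This stands and limits the weight of the point.
- **Recent nitroglycerin use may be low.** The Diagnostic criteria describe nitroglycerin as ineffective in these patients. Bias also needs intake close to a single scheduled draw, not merely fewer attacks over 12 weeks. This stands. Lack of symptom relief does not stop a tablet from supplying NO, but it makes a large difference between arms less certain.
- **The randomised contrast is valid for what it estimates.** The difference in circulating NO is the total effect of assignment, and reduced rescue use is one of its pathways. This stands. The difficulty lies in calling that contrast endothelial function.

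A reader might infer that the NO result is biased against QJHX, or will come out with the wrong sign. The documents do not support this. With equal recent use the bias is zero, and reversal occurs only at the extreme of the assumed range. A reader might also infer that restricting to patients without maintenance nitrates gives a clean endothelial reading. It does not, because those patients may still take nitroglycerin for attacks.

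**Conclusion.** The concern holds in a limited form. The stated raw comparison of NO is less precise than data the trial already collects would allow, and its result cannot be read directly as endothelial function.

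The noise from maintenance nitrates is the firmer part. Under the assumed range (20% to 50% users, shift 0.5 to 2 SD), power falls from 90% to between 89% and 63%, and the 63% needs both inputs at their upper ends. Bias from as-needed nitroglycerin is possible and would run against QJHX if control patients had more recent intake at the week-12 draw. Its size cannot be determined from the documents: the article gives no usage rate, assay or time from dose to draw. The −0.025 to −0.40 SD in step 3 follows from assumed inputs and is not an estimate.

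The primary outcomes, safety assessment and sample size do not depend on this.

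**What to change.** 1. Compare week-12 NO between arms by ANCOVA, with baseline NO and baseline maintenance nitrate use (yes/no) as covariates, in place of the raw two-sample test. Both covariates precede randomisation.
2. Report maintenance nitrate and nitroglycerin use by arm from the concomitant-medication record.
3. Where the time of last intake before the draw is available, add a sensitivity analysis that excludes recently dosed samples. Fix the window before data review, and label the analysis as conditioning on a post-randomisation event. Do not adjust the main analysis for nitroglycerin use, which would itself introduce bias.
4. State that the NO contrast is the total effect of assignment on circulating NO and is only supportive evidence on endothelial function, including in patients without maintenance nitrates.

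Items 1, 2 and 4 need a few lines of analysis text and no new sample or visit, provided baseline nitrate use was recorded as the article describes. Item 3 needs one case-report-form field and can cover future draws only. Trial status reports 83 of 150 patients (55%) already recruited, so baseline draws already taken cannot be covered prospectively, nor can any completed week-12 draws. That analysis will be incomplete.

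No change to any treatment or rescue rule is proposed.
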